# Effectiveness and cost-effectiveness of Improving clinicians’ diagnostic and communication Skills on Antibiotic prescribing Appropriateness in patients with acute Cough in primary care in CATalonia (the ISAAC-CAT study): study protocol for a cluster randomised controlled trial

**DOI:** 10.1186/s13063-019-3727-3

**Published:** 2019-12-17

**Keywords:** Cost-effectiveness, Cost-utility, Effectiveness, Anti-bacterial agents, Prescribing, Acute cough, Respiratory tract infections, Antimicrobial stewardship, Qualitative research, Incremental cost-utility ratio, Primary healthcare

## Abstract

**Background:**

Despite their marginal benefit, about 60% of acute lower respiratory tract infections (ALRTIs) are currently treated with antibiotics in Catalonia. This study aims to evaluate the effectiveness and efficiency of a continuous disease-focused intervention (C-reactive protein [CRP]) and an illness-focused intervention (enhancement of communication skills to optimise doctor-patient consultations) on antibiotic prescribing in patients with ALRTIs in Catalan primary care centres.

**Methods/design:**

A cluster randomised, factorial, controlled trial aimed at including 20 primary care centres (*N* = 2940 patients) with patients older than 18 years of age presenting for a first consultation with an ALRTI will be included in the study. Primary care centres will be identified on the basis of socioeconomic data and antibiotic consumption. Centres will be randomly assigned according to hierarchical clustering to any of four trial arms: usual care, CRP testing, enhanced communication skills backed up with patient leaflets, or combined interventions. A cost-effectiveness and cost-utility analysis will be performed from the societal and national healthcare system perspectives, and the time horizon of the analysis will be 1 year. Two qualitative studies (pre- and post-clinical trial) aimed to identify the expectations and concerns of patients with ALRTIs and the barriers and facilitators of each intervention arm will be run. Family doctors and nurses assigned to the interventions will participate in a 2-h training workshop before the inception of the trial and will receive a monthly intervention-tailored training module during the year of the trial period. Primary outcomes will be antibiotic use within the first 6 weeks, duration of moderate to severe cough, and the quality-adjusted life-years. Secondary outcomes will be duration of illness and severity of cough measured using a symptom diary, healthcare re-consultations, hospital admissions, and complications. Healthcare costs will be considered and expressed in 2021 euros (year foreseen to finalise the study) of the current year of the analysis. Univariate and multivariate sensitivity analyses will be carried out.

**Discussion:**

The ISAAC-CAT project will contribute to evaluate the effectiveness and efficiency of different strategies for more appropriate antibiotic prescribing that are currently out of the scope of the actual clinical guidelines.

**Trial registration:**

ClinicalTrials.gov, NCT03931577.

## Background

Overuse of antibiotics has contributed to the development of antimicrobial resistance, which represents a major threat to human health worldwide [1]. In addition to driving resistance, non-indicated use of antibiotics incurs costs, increases re-consultation for subsequent episodes, medicalizes self-limiting illness, and unnecessarily exposes individuals to the risk of side effects. Most antibiotics are prescribed in primary care, most commonly for acute lower respiratory tract infections (ALRTI), which account for one-fourth of all the infectious diseases treated by general practitioners (GPs). According to a study carried out in Catalonia, about 60% of ALRTIs are currently treated with antibiotics [2]. The latest Cochrane review also suggests that only a slight benefit is achieved from the prescription of antibiotics [3]. Because no new classes of antibiotics have been developed in the last two decades, rationalisation of antibiotic use in the treatment of ALRTIs in primary care is a key target for influencing the antibiotic-prescribing behaviour of clinicians [1]. This supports the case for strategies that promote a more prudent use of antibiotics for these infections. This is even more important in Catalonia, because this is one of the European Union countries with the highest rates of antibiotic prescribing, which has even slightly increased in the last years [4, 5]. This finding is also supported by the results of the latest Eurobarometer on antibiotic use carried out in 2016, in which 47% of the Spanish respondents admitted having taken an antibiotic in the previous year [6].

Antibiotic use can be improved by using educational interventions such as dissemination of printed and audio-visual educational materials, group education, personal or group feedback, individual outreach visits, reminders at the time of prescribing, and computer-assisted decision-making systems, among others, but these interventions generally result in little change in prescription practices, although the effect is greater with multi-faceted approaches [7, 8]. In a recent Cochrane review of systematic reviews aimed at assessing the effects of interventions targeting clinician antibiotic prescribing for ALRTIs in primary care, the reviewers found that the most powerful tools for reducing unnecessary antibiotic prescribing are C-reactive protein (CRP) rapid testing, shared decision making, and procalcitonin-guided management without compromising outcomes of patient satisfaction and re-consultation, although the measurement of these outcomes was limited in the trials [9].

The antibiotic prescribing behaviour of GPs for acute cough in adults is influenced by their perceptions of patient expectations, but sometimes their perceptions do not match patient views [10]. Patients report lower levels of satisfaction with their consultation if they have an expectation for antibiotics that is not met, and being able to effectively elicit patient views towards shared decisions is therefore an important skill for clinicians managing acute cough. Interactive workshops for healthcare professionals and education of patients are likely to lower the rate of antibiotic prescribing [10]. A Dutch study found that the training of physicians in advanced communication skills by seminar role-playing and peer feedback on consultation transcripts reduced antibiotic prescribing rates by 20% [11]. In a Welsh study a 4% reduction in global antibiotic use was found after web-based training in advanced communication skills [12].

CRP testing has been shown to safely reduce antibiotic prescribing in primary care [13]. In a Dutch study, training of physicians in CRP testing lowered the rate of antibiotic prescribing by 20%, but the greatest reduction was observed among GPs assigned to CRP testing and enhanced communication skills training [11]. In a multinational study conducted in Europe, which assessed the effects of internet-based training on antibiotic prescribing for acute respiratory tract infections, both CRP and clinician training in communication skills were effective in reducing antibiotic prescribing, but the greatest reduction was also seen when both the CRP testing and communication skills training interventions were combined [14]. The effect of the communication skills training was greater in the Dutch study, which could be explained mainly by the fact that the intervention was more intense and continuous. In the latter study, however, the intervention was limited to a single online training lasting approximately 1 h before the trial started. In addition, patients were followed for only 4 weeks, whereas approximately 25% of patients still have cough after this period, and patients still re-attended their GPs because full recovery was not accomplished.

Recent evidence showed that ambulatory antibiotic prescription is associated with a hidden cost of antibiotic resistance that substantially increases the cost of an antibiotic prescription [15]. This finding raises concerns regarding the magnitude of misalignment between individual and societal antibiotic costs. There is a lack of evidence evaluating the efficiency of different multi-faceted approaches in order to decrease the inappropriate prescribing of antibiotics in Mediterranean countries. Although CRP point-of-care tests are widely used in a number of European countries for the management of ALRTIs, they are not yet routinely used in Catalonia. In addition, these overprescribing actions could lead to inefficiencies of the health system.

## Methods/design

### Objectives

This study aims to evaluate the effectiveness and efficiency of a continuous (workshop and monthly web-based training) disease-focused intervention (CRP testing) and a continuous (on-site and monthly online training) illness-focused intervention (enhancement of communication skills to optimise doctor-patient consultations and share decision making with the aid of patient-centred leaflets) on antibiotic prescribing in patients with ALRTIs in Catalan primary care centres. An economic evaluation of four strategies for reducing antibiotic prescribing will be performed. Particularly, a cost-effectiveness and cost-utility analysis will be conducted. These interventions will be compared with the current antibiotic prescribing strategy used in the primary care centres. The analysis will be conducted from the societal and the national healthcare system perspectives. Two qualitative studies (pre- and post-clinical trial) will be also conducted to inform the development and evaluation of the clinical trial.

### Study design

A cluster randomised, factorial, controlled trial performed over a period of 18 months including two autumn-winter seasons will be carried out. A randomised cluster design will be used to keep contamination (influence on participants’ behaviour when another participant or physician alters his/her behaviour) within primary care centres to a minimum, because three GPs and nurses per centre are expected to participate and because a centre-based meeting is part of the intervention. Patients who fulfil the inclusion criteria will be given written and verbal information about the study and will be asked to provide written informed consent.

The inclusion criteria will be age older than 18 years and first consultation for acute cough (new cough or worsening of a previous cough) of up to 3 weeks’ duration as the predominant symptom, which the clinician believes to be an infectious ALRTI, as defined in other studies [3]. The exclusion criteria will be a working diagnosis of a non-infective disorder, such as heart failure, pulmonary embolus, oesophageal reflux, or allergy; use of antibiotics in the previous 2 weeks; immunological deficiencies; and/or inability to provide informed consent or unable to follow the study procedures. Pneumonia and acute exacerbations of chronic obstructive pulmonary disease will not be deemed as exclusion criteria, because they are included in the ALRTI definition. The Standard Protocol Items: Recommendation for Interventional Trials (SPIRIT) Checklist is provided as Additional file 1.

### Sample size calculation

To calculate the sample size, we will use a type I error of 5% and a power of 80%, and we will assume that antibiotic prescribing will decrease by at least 15%, from 60% to 45%, in any one of the three intervention groups. We will also assume a drop-out rate of 12% and an intra-cluster correlation coefficient for antibiotic prescribing within practices of up to 0.07, based on two recent studies [14, 16]. We estimate that a sample of 788 (197 × 4) patients will be needed. Allowance for an inflation factor of 3.73 due to clustering and rounding of numbers for the four subgroups give an overall sample size of 2940 [17]. As a consequence, at least 147 patients will be recruited per centre.

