### Setting and timing

General practices throughout Catalonia in the localities of the study centres (with different socioeconomic levels) will be approached, and at least three pairs of clinicians (GPs and nurses) in eligible centres will be invited to participate. Eligible centres will be stratified depending on the socioeconomic level and baseline antibiotic consumption, and only those that had not previously used any intervention to reduce antibiotic prescribing rates will be selected. They are expected to include 150 patients (75 patients in each autumn-winter season) in the trial.

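### The clustering inflation factor of 3.73 fits 40 patients per centre, not the planned 147; at the stated ICC, 20 centres give about 33–41% power for the sized comparison, not 80%

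*Protocol article*

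**What the plan says.** All the inputs are printed in the protocol article.

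- **Effect, error rates and drop-out** (Sample size calculation): type I error 5%, power 80%, drop-out 12%, and the assumption that "antibiotic prescribing will decrease by at least 15%, from 60% to 45%, in any one of the three intervention groups".
- **Clustering** (same section): an "intra-cluster correlation coefficient for antibiotic prescribing within practices of up to 0.07".
- **Inflation** (same section): 197 patients per arm, 788 in total, before clustering. Then "Allowance for an inflation factor of 3.73 due to clustering and rounding of numbers for the four subgroups" give 2940.
- **Patients per centre** (same section): "As a consequence, at least 147 patients will be recruited per centre". Setting and timing gives nearly the same number: "They are expected to include 150 patients (75 patients in each autumn-winter season) in the trial".
- **Number of clusters** (Abstract, Methods/design): "A cluster randomised, factorial, controlled trial aimed at including 20 primary care centres". Trial interventions confirms that centres are the randomised units and that there are four arms, so five centres per arm if the split is equal.

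**The concern.** The inflation factor depends on the number of patients per cluster. Here it is used to obtain a total, the total is divided by 20 centres, and the resulting cluster size is not the one the factor assumes. Two consecutive sentences of one paragraph are therefore incompatible: 3.73 produces 2940, and 2940 patients in 20 centres invalidate 3.73.

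Antibiotic use within six weeks is a primary outcome. If the true power is far below 80%, a non-significant result would be read as evidence against a 15-point effect when the trial had little chance of detecting one.

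**Working it through.** **1. Reproducing the protocol's figures.** Two-sided 5% test, 80% power, 60% vs 45%, pooled variance under the null, mean proportion 0.525:

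n = [1.960 × √(2 × 0.525 × 0.475) + 0.842 × √(0.24 + 0.2475)]² / 0.15² = 172.8, so 173 per arm.

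- Drop-out: 173 / 0.88 = 196.6, so 197 per arm.
- Four arms: 4 × 197 = 788.
- Clustering: 788 × 3.73 = 2939.2, rounded to 2940.
- Per centre: 2940 / 20 = 147.

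Every printed number is recovered, so the method is clear and only the factor is in question.

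**2. What 3.73 implies.** With DE = 1 + (m − 1) × ICC and ICC = 0.07:

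m = (3.73 − 1) / 0.07 + 1 = 40.

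The protocol nowhere mentions 40 patients per cluster. That 40 was the value used is an inference from the exact match; the mismatch does not depend on it.

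**3. The factor at the planned cluster size.**

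| Patients per cluster | DE at ICC 0.07 |
|---|---|
| 40 | 3.73 |
| 49 (147 / 3 GPs) | 4.36 |
| 129 (147 × 0.88, completers) | 9.96 |
| 147 | 11.22 |
| 150 | 11.43 |

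The GP row shows that treating GPs as the clusters does not give 3.73 either. In any case the ICC is stated for practices and randomisation is by centre.

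**4. Effective sample size per arm.** Five centres, 129 completers each: 5 × 129 / 9.96 = 64.8, against the 173 required. As m grows without limit, this tends to 5 / 0.07 = 71.4.

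**5. Power for one arm against usual care, 60% vs 45%, unadjusted.** SE = √(0.4875 / 64.8) = 0.0867.

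| Method | Power | Difference detectable with 80% power |
|---|---|---|
| Normal: Φ(0.15 / 0.0867 − 1.96) | 41% | 24 points |
| Noncentral t, 16 df (centre variance from all four arms) | 37% | 25 points |
| Noncentral t, 8 df (two arms only) | 33% | 27 points |

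With unlimited patients per centre, normal-approximation power is still only 44%. With 40 patients per centre in the same 20 centres it would be about 35%. The limit is the number of centres.

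**6. Dependence on the ICC** (129 completers per centre, same comparison; t test with 8 df to normal approximation).

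| ICC | Power |
|---|---|
| 0.07 | 33–41% |
| 0.05 | 42–52% |
| 0.03 | 59–70% |
| 0.02 | 72–82% |

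Eighty per cent is reached at an ICC of about 0.022 (normal), 0.018 (t, 16 df) or 0.015 (t, 8 df). Using 147 rather than 129 per centre moves these to 0.023, 0.019 and 0.016.

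**7. Centres needed at ICC 0.07.** 173 × 9.96 / 129 = 13.4, so about 14 per arm, or 56 in all.

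**The case against.** Four points can be made for the protocol.

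- **The trial is factorial.** Statistical analysis reports main effects if interactions are not significant, which compares 10 centres with 10. On the same inputs, with the full 15-point effect at both levels of the other factor, power is 69% (normal) or 64% (t, 18 df). This is a real qualification: 33–41% is not the power of every planned analysis. But the sample size section sizes single arms against usual care (197 × 4), the pooling is conditional, and 64–69% is still short of 80%.
- **The ICC is an upper bound.** The wording is up to 0.07, and step 6 shows how power rises as the ICC falls. However, the printed factor fits 0.07 with 40 per cluster, and the protocol neither states nor justifies a value near 0.02.
- **Baseline prescribing is taken into account.** Centres are stratified by socioeconomic level and antibiotic consumption, and the analysis adjusts for the baseline prescribing rate. Both may reduce between-centre variance. The gain cannot be judged because no figure is given, and the sample size section claims none.
- **The design can hardly change.** Randomisation was set for 21 October 2019 and recruitment opened on 18 November 2019, before publication. Adding centres would mean more training and devices. This bears on the remedy, not on whether the stated power is correct.

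**Conclusion.** The concern holds: the calculation is wrong as written. The factor of 3.73 does not belong to 147 patients per centre at ICC 0.07; the correct value is 11.22 at recruitment, or 9.96 among completers. For the comparison the protocol sized, power is about 33–41% rather than 80%, and the detectable difference is 24–27 points rather than 15. These figures assume five equal centres per arm, 12% drop-out, ICC 0.07, a two-sided 5% test and no gain from covariate adjustment. Smaller ICCs or the main-effects analysis give higher power, but nothing in the document restores 80% at the ICC it states.

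**What to change.** In the sample size section, replace 3.73 with the design effect for the planned cluster size, 1 + (147 − 1) × 0.07 = 11.22, and state the cluster size used. Then do one of the following:

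- Restate what 20 centres deliver at ICC 0.07: about 33–41% power for 60% vs 45% in one arm against usual care, with a detectable difference of about 24–27 points, naming the test and degrees of freedom. If the main-effects analysis is to carry the power claim, give its figure separately, with the no-interaction assumption.
- Or state the lower ICC on which 80% power for the arm-versus-usual-care comparison depends (about 0.015–0.023, according to the test) and justify it, including any reduction expected from baseline adjustment.

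Either change is a rewording and needs no extra patients or centres. Its price is a less favourable power statement, and a non-significant arm comparison would have to be reported as inconclusive about a 15-point effect unless the confidence interval excludes it.

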### Setting and timing

General practices throughout Catalonia in the localities of the study centres (with different socioeconomic levels) will be approached, and at least three pairs of clinicians (GPs and nurses) in eligible centres will be invited to participate. Eligible centres will be stratified depending on the socioeconomic level and baseline antibiotic consumption, and only those that had not previously used any intervention to reduce antibiotic prescribing rates will be selected. They are expected to include 150 patients (75 patients in each autumn-winter season) in the trial.

### Trial interventions

The centres will be randomly assigned to four trial arms: usual care, training in the use of a point-of-care CRP test, training in enhanced communication skills, or combined training in CRP testing and enhanced communication skills (Fig. 1). Masking of GPs or patients to the intervention itself is not possible. Randomisation of primary care centres will be achieved by computer generation of random numbers.

**Fig. 1 Fig1:**
[figure not shown]
Flowchart of the randomised clinical trial. *ALRTI* acute lower respiratory tract infection

An on-the-spot 2-h training workshop will take place in the different areas before the inception of the trial. This training will be followed by monthly internet-based short training capsules tailored to either of the two interventions measured (clinical cases, medical literature, reminders) that GPs allocated to this intervention will have to attend and answer. GPs assigned to both interventions will receive the two training programmes. The usual care group will assess and manage patients according to the practice’s normal procedures.

The CRP group will receive internet training on how to target testing (e.g., in cases of clinical uncertainty, such as in patients with abnormal auscultation, dyspnoea, and impairment of vital signs) and how to negotiate with the patient about management decisions. The tests will be carried out with Afinion 2 CRP devices (Abbott Diagnostics, Lake Forest, IL, USA). Clinicians (GPs and nurses) will practise using the device during a run-in period of 2 weeks before data collection starts. GPs will be informed about the updated recommendations on how to interpret the CRP values and the evidence-based management (no antibiotics, delayed antibiotic prescribing or immediate antibiotic prescribing). Training in enhanced communication skills will focus on the gathering of information on patients’ concerns and expectations, exchange of information on symptoms, natural disease course and treatments, agreement of a management plan, red flags, and providing guidance about when to re-consult and summing up. GPs will also be provided with an interactive booklet to use during consultations that includes information on symptoms, use of antibiotics and antibiotic resistance, self-help measures, and when to re-consult, and the booklet will be given to the patient. This training will be supported by video demonstrations of consultation techniques. GPs will also be informed about the updated recommendations on management of ALRTIs.

### Outcome measures

During the index consultation GPs will document the duration of the illness, the severity of cough and other symptoms (rated 0, not problematic; to 6, severely problematic), and the severity of the infections. After randomisation a more detailed case report form (CRF) will be used in the follow-up consultations and will include the same details as the index form plus medical history, current medications, smoking status, findings of structured examination, whether CRP is tested, and whether the booklet is used. The primary outcome measures will be antibiotic consumption within the first 6 weeks, as documented in the CRFs and double-checked by the Pharmacy Unit of the Catalan Institute of Health, which can track if the antibiotic has been dispensed at any of the Catalan pharmacies; the duration of moderate to severe cough (i.e., those rating their cough as 3 or more by means of a Likert scale); and the quality-adjusted life-years (QALYs), which will be collected by means of the EQ-5D-5L questionnaire within the first 6 weeks (Table 1).

**Table 1 Tab1:** Schedule of enrolment, interventions and assessments for the clinical trial

Time point	Study period November 4, 2019–April 30, 2021		
	Day 1	Week 2	Week 6
Enrolment			
Medical history and physical examination	X		
Explanation of the study and informed consent	X		
Initial CRF	X		
Giving out of the symptom diary, up to week 2	X		
Interventions			
CRP rapid test if needed (only among those patients visited by professionals assigned to the CRP intervention groups)*	X		
Use of an interactive booklet (only among those patients visited by professionals assigned to the enhanced communication skill intervention groups)*	X		
Assessments			
Assessment of the clinical outcome		X	X
Collection and review of the symptom diary		X	
EQ-5D-5L questionnaire	X	X	X
Antibiotic consumption	X	X	X
Use of drugs other than antibiotics	X	X	X
Tests ordered by clinicians	X	X	X
Patient satisfaction with care		X	X
Patient perception of the usefulness of the information received		X	X
Patient future consulting intentions		X	X
Absenteeism	X	X	X
Evaluation of adverse events		X	X
Number of re-consultations to primary and secondary care and number of complications regarding the ALRTI			X

*Abbreviations: ALRTI* acute lower respiratory tract infection, *CRF* case report form, *CRP* C-reactive protein, *GP* general practitioner

Randomisation will take place 2 weeks before initiating the clinical trial (October 21, 2019). Workshop for GPs and nurses assigned to any of the three intervention arms at the end of October 2019

*Monthly internet-based short training capsules for GPs and nurses assigned to any of the intervention groups

Secondary outcome measures are listed in Table 2. The duration of symptoms rated moderate to severe will also be recorded. Because this study will follow patients for 6 weeks, we will be able to better define the duration of acute cough due to ALRTI. Symptoms will be rated daily as 0 (no problem) to 6 (as bad as it could be) until they resolve, and the information will be reported by patients in self-completed diaries, similar to what was done in a recent clinical trial on delayed antibiotic prescribing carried out in Catalonia [18]. For patients who do not return diaries, a short form asking about the details of the duration and severity of symptoms and whether antibiotics have been taken or whether the booklet has been used will be completed by telephone call to the patient.

**Table 2 Tab2:** Secondary objectives and outcome measures

Objectives	Outcome measures	Time point(s) of evaluation of this outcome measure
Number of re-consultations to primary and secondary care and number of complications regarding the ALRTI	Re-consultation for new or worsening symptoms, new signs, or hospital admission, assessed by review of medical notes (practice staff, the local study team, or both using a standard form to report these data), and number of complications regarding the ALRTI	First 6 weeks post-randomisation
Duration of moderate to severe symptoms	Number of days until the last day any of the symptoms is rated 3 or more. Symptoms will be rated daily as 0 (no problem) to 6 (as bad as it could be) until they resolve, and the information will be reported by patients in self-completed diaries.	First 6 weeks post-randomisation
Antibiotic prescription at the baseline visit, differentiating immediate and delayed antibiotic prescribing, and antibiotic dispensing at the pharmacies	Reported in the CRF. The number of patients treated with immediate and delayed antibiotic prescribing will be evaluated. Dispensing of the antibiotics at the pharmacies.	Baseline visit. The dispensing of antibiotics will be tracked in the first 6 weeks post-randomisation.
Drugs other than antibiotics	Reported by patients in self-completed diaries	First 6 weeks post-randomisation
Tests ordered by clinicians	Reported in the CRF	Baseline visit
Patient satisfaction with care	Reported in the symptom diaries	First 6 weeks post-randomisation
Patient perception of the usefulness of the information received	Collected in the symptom diaries	First 6 weeks post-randomisation
Patient future consulting intentions	Collected in the symptom diaries	First 6 weeks post-randomisation
Serious adverse events	Assessed by review of medical notes (practice staff, the local study team, or both using a standard form to report these data)	First 6 weeks post-randomisation
Number of days of sick leave (absenteeism)	Collected in the CRFs	First 6 weeks post-randomisation

*ALRTI* acute lower respiratory tract infection, *CRF* case report form

The data collection process and the rest of the study procedures will be supervised. A clinical research associate will perform periodic visits to the sites and provide online supervision of the data. A data monitoring committee has been deemed not necessary because of the study characteristics, as well as external audits. Nevertheless, the coordinating team will hold periodic meetings, and study procedures will be reviewed.

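### Table 1 ends and collects the symptom diary at week 2, but the outcome text and Table 2 need it to run to resolution within 6 weeks; if Table 1 governs, diary-based durations are censored at about day 14

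*Protocol article*

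**What the plan says.** All of this is in the protocol article, mostly under Outcome measures.

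- **Schedule (Table 1).** The Day 1 entry reads "Giving out of the symptom diary, up to week 2". The row "Collection and review of the symptom diary" has one mark, at week 2, and none at week 6.
- **Primary outcome.** One of three primary outcomes is "the duration of moderate to severe cough (i.e., those rating their cough as 3 or more by means of a Likert scale". That clause gives neither a time window nor an instrument.
- **Text after Table 1.** "Symptoms will be rated daily as 0 (no problem) to 6 (as bad as it could be) until they resolve", with patients entering the scores in their own diaries. The same paragraph says: "Because this study will follow patients for 6 weeks, we will be able to better define the duration of acute cough due to ALRTI".
- **Table 2.** The secondary outcome on moderate-to-severe symptoms is defined as "Number of days until the last day any of the symptoms is rated 3 or more", taken from the same diaries, with a 6-week window.
- **Fallback.** A short telephone form asks about duration and severity, but only for patients whose diary is not returned.
- **Background.** A previous multinational trial is faulted for 4 weeks of follow-up because "approximately 25% of patients still have cough after this period".

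**The concern.** A diary handed in at week 2 cannot show the last day on which a symptom scored 3 or above if that day falls in weeks 3 to 6. The schedule table is what sites work from. If they follow it, the daily scores that the duration outcomes need will not exist for patients who are still unwell at week 2, and no analysis plan can recover them.

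The gap reaches a primary outcome, because the diary is the only daily symptom rating described. A 14-day diary would also be shorter than the 4 weeks that the protocol itself considers too short for cough. If mean days are compared on such data, a real difference between arms in prolonged cough shrinks towards zero.

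**Working it through.** **Is there a figure to reproduce?** The protocol gives no effect size, standard deviation or sample size for cough duration. Its stated total rests on antibiotic prescribing alone: 60% versus 45%, two-sided 5%, 80% power gives 173 per arm; 173 / (1 − 0.12) = 197; 197 × 4 = 788; 788 × 3.73 = 2939, against 2940 stated. It reproduces and does not depend on the diary period.

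**The sources side by side**

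| Source | How long the diary runs | Collected |
|---|---|---|
| Table 1 | to week 2 | week 2 only |
| Text after Table 1 | daily until resolution | not stated |
| Table 2, symptom duration | 6-week window | not stated |

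The wording of the Day 1 row and the single collection mark agree with each other, so a broken table is an unlikely explanation. Table 2 also takes satisfaction, usefulness of information and consulting intentions from the diary over 6 weeks. Table 1 marks these at week 6, after the diary has been collected.

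**Can another source fill weeks 3 to 6?**

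- Telephone form: a patient who returns a 2-week diary while still coughing does not qualify for it.
- Week-6 clinical outcome assessment: scheduled, but its content is not defined.
- Follow-up case report form: repeats the index items, which include illness duration and cough severity, but is not named as the source of this endpoint.

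**Size if Table 1 governs**

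Input from the protocol: about 25% still coughing after 4 weeks (any cough). Everyone in that group has outlasted a 14-day diary, so at least 25% are censored for any cough. The share still scoring 3 or more is not given, so I assume a range.

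Assumptions: exponential durations from Day 1; S(28) of 0.25, 0.10, 0.05 or 0.02; a comparison arm with a 20% longer mean.

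- Rate: λ = −ln S(28) / 28; comparison arm λ / 1.2
- Unresolved at day 14: S(14) = exp(−14λ)
- Restricted mean to day t: (1 − exp(−λt)) / λ
- Patients left after drop-out: 2940 × 0.88 = 2587

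For S(28) = 0.25: λ = 1.3863 / 28 = 0.0495 and S(14) = 0.50. The restricted mean is 10.10 days to day 14 and 17.67 days to day 42.

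| S(28) | Unresolved at day 14 | Patients (of 2587) | Difference to day 14 (days) | Difference to day 42 (days) | Share kept |
|---|---|---|---|---|---|
| 0.25 | 50% | about 1290 | 0.54 | 2.28 | 23% |
| 0.10 | 32% | about 820 | 0.69 | 2.00 | 34% |
| 0.05 | 22% | about 580 | 0.74 | 1.71 | 43% |
| 0.02 | 14% | about 370 | 0.76 | 1.39 | 55% |

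**The case against.** The strongest reply is that the day-14 cut is not established. The text and Table 2 both say otherwise, and the document does not say which governs. This stands: censoring is a consequence of following Table 1, not a stated design.

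Four further points also stand, and each limits what a reader might infer.

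- **That the primary cough outcome is defined over 6 weeks by diary.** Its clause names neither. The explicit 6-week diary definition belongs to the secondary symptom-duration outcome. For cough, both are reasonable inferences from the text after Table 1.
- **That nothing is known after week 2.** A week-6 contact exists, and the telephone form shows that the protocol accepts duration reports that are not daily. What is missing is a statement that either the week-6 assessment or the follow-up form supplies the endpoint. The same holds for satisfaction and the related items: collection at week 6 is scheduled, and only the instrument is unclear.
- **That the effect is attenuated at least four-fold.** That applies the 25% for any cough to an endpoint of cough scored 3 or more. It also concerns restricted means only. Under the exponential assumption, a censored time-to-event analysis would leave the hazard ratio unbiased and lose precision: resolutions observed fall from 87.5% to 50% at S(28) = 0.25, and from 99.7% to 85.9% at S(28) = 0.02.
- **That the whole 6-week advantage, or the safety case, is lost.** Antibiotic use, EQ-5D-5L and the outcomes from medical notes still run to week 6. The protocol does not call cough duration its check on harm.

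Two other criticisms are tempting but not supported. The Statistical analysis section allows error distributions to vary with the objective, and the handling of censored durations is ordinary analysis-plan detail. And although Table 2 counts from randomisation, which for centres is one calendar date in October 2019, Table 1 clearly schedules each patient from Day 1.

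None of this removes the contradiction over how long the diary runs.

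**Conclusion.** The point holds as an internal contradiction with a conditional consequence. Table 1 stops and collects the diary at week 2; the text and Table 2 need it until resolution within 6 weeks. If Table 1 is followed, diary-based durations are right-censored at about day 14, with no named source for later days.

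The only size the protocol itself supports is a floor of roughly 25% of patients outlasting the diary for any cough. For moderate-to-severe cough, the 14% to 50% unresolved at day 14, and the 23% to 55% of the 42-day difference kept, depend on exponential durations, on the assumed 2% to 25% unresolved at day 28, on a 20% longer mean, and on a comparison of restricted mean days. Even at the mild end, nearly half of the difference is lost. The stated sample size is unaffected.

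**What to change.** Reconcile Table 1 with the text and Table 2 in one of two ways.

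1. Run the diary until symptoms resolve or week 6, whichever comes first, and collect it at week 6, keeping the week-2 review.
2. Keep the 2-week diary, and for patients unresolved at week 2 record at the existing week-6 contact the last day on which cough, and any symptom, scored 3 or above. Name that record as the source of the endpoint.

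In either case, state a 6-week window for the primary cough outcome, counted from each patient's Day 1. If the diary has to stop at week 2 with nothing added, restate the cough and symptom-duration outcomes as 14-day censored outcomes.

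The cost is small because a week-6 contact is already scheduled. The first option adds some patient burden and will leave some later diary days missing. The second is lighter, but replaces daily scores with recall for weeks 3 to 6.
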